## Abstract

**Background:**

Major depressive disorder (MDD) imposes a considerable disease burden on individuals and societies. Web-based interventions have shown to be effective in reducing depressive symptom severity. However, it is not known whether web-based interventions may also be effective in preventing the onset of MDD. The aim of this study is to evaluate the (cost-) effectiveness of an indicated web-based guided self-help intervention (GET.ON Mood Enhancer Prevention) on the onset of MDD.

**Methods/Design:**

A randomised controlled trial (RCT) will be conducted to compare the (cost-) effectiveness of the GET.ON Mood Enhancer Prevention training with a control condition exclusively receiving online-based psychoeducation on depression. Adults with subthreshold depression (N = 406) will be recruited from the general population and randomised to one of the two conditions. The primary outcome is time to onset of MDD within a 12-months follow-up period. MDD will be assessed according to DSM-IV criteria as assessed by the telephone-administered Structured Clinical Interview for DSM-IV (SCID). Time to onset of MDD will be assessed using life charts. Secondary outcomes include changes on various indicators of depressive symptom severity, anxiety and quality of life from baseline to post-treatment, to a 6-month and a 12-month follow up. Additionally, an economic evaluation using a societal perspective will be conducted to examine the intervention’s cost-effectiveness.

**Discussion:**

This is one of the first randomised controlled trials that examines the effect of an indicated guided self-help web-based intervention on the incidence of major depression. If shown to be effective, the intervention will contribute to reducing the disease burden due to MDD in the general population.

**Trial registration:**

German Clinical Trial Registration DRKS00004709.

## Background

Major depressive disorder (MDD) is highly prevalent [1,2] and has an incidence rate that is high relative to the number of prevalent cases [3]. The global point prevalence is estimated at 4.7% with an annual incidence rate of 3% [4]. Moreover, MDD is related to poorer quality of life [5,6], increased mortality [7], and substantial economic costs [8-10]. Currently, MDD ranks as the fourth disorder with the highest disease burden and is projected to be the leading cause of premature mortality and disability in high-income countries by 2030 [11].

The disease burden attributable to MDD might be reduced in two ways. The first approach is to treat existing cases. But despite the availability of effective MDD treatments, such as face-to-face cognitive-behaviour therapy, behavioural activation therapy or problem-solving therapy [12-14] less than half of depressed patients are recognised and treated [15]. Furthermore, it is estimated that approximately only one third of the disease burden caused by MDD could be averted assuming the hypothetical scenario of 100% coverage and full compliance to evidence-based treatments [16,17].

The second approach is reducing the development of new cases, which requires prevention. Preventive interventions might be capable of contributing to a further reduction in disease burden. A recent meta-analysis of 19 randomised controlled trials demonstrated that preventive interventions based on cognitive behaviour or interpersonal therapy were able to reduce the incidence of MDD by 22% [18]. One of these studies also showed the effectiveness of minimal contact cognitive-behavioural therapy for depression, based on the ‘Coping with Depression’ course [19].

Selective prevention aimed at high-risk groups and indicated preventive efforts that target individuals who show already detectable signs of MDD but who do not yet meet the diagnostic criteria for the disorder were particularly effective. Universal prevention aimed at the general population regardless of any risk profile showed only small effects.

Indicated prevention has been suggested to be more “efficient” than selective prevention [20]. “Efficiency” is here defined in terms of “impact”, that is the number of cases that would be prevented if the targeted risk indicator were fully blocked in the population and “effort” reflecting the number needed to be treated to prevent one new case of MDD. From a clinical point of view, indicated prevention is worthwhile for two reasons. First, subthreshold depression is a highly prevalent condition [21] and the burden posed on people affected and the community is considerable [22,23]. Second, subthreshold depression is a risk indicator for MDD, as the incidence rate of MDD is significantly increased in subjects with subthreshold depression compared to those without ranging from .15 in a general population up to .58 in general medical populations and high risk groups [24].

Despite their effectiveness, currently available indicated preventive face-to-face interventions face some serious limitations. These include (a) difficulties delivering interventions to the community *en masse* due to constraints in the workforce and health care resources [25,26], (b) limited availability of evidence-based interventions and clinicians in routine practice, especially in rural areas, and (c) low participation rates even if access to those interventions is at little or no costs [27]. Therefore, new approaches are needed to enhance the impact of indicated preventive interventions.

Using the Internet to provide (guided) self-help interventions may help to overcome some of the limitations of traditional preventive services. Web-based guided self-help strategies have several advantages over face-to-face approaches. These include: (a) interventions are more easily accessible at any time and place, (b) anonymity is assured when patients want to avoid stigmatisation, (c) a greater potential for the integration of acquired skills in daily life due to an emphasis on the participants’ active role in (guided) self-help interventions [28] (d) participants can work at their own pace and go through materials as often as they want, and (e) elimination of travel time and costs for both participants and clinicians. Finally (f), web-based interventions are easily scalable implying that only a small increase in therapeutic resources is required for reaching a greater proportion of the eligible population using these interventions. Thus, marginal costs per additional user are low due to an economies of scale effect.

Web-based interventions have shown to be well accepted by participants [29,30] and to be effective in the acute treatment of MDD [12] as well as in reducing depressive symptoms both in adults and adolescents [31,32]. However, although several web-based interventions are labelled as preventive interventions, i.e. ‘Colour your life’ [33,34], to the best of our knowledge, no study has yet investigated the (cost-) effectiveness of an indicated guided self-help web-based preventive intervention on the onset of diagnosed major depressive disorders.

### Objective and research questions

The aim of this study is to evaluate whether a newly developed indicated guided self-help web-based intervention (GET.ON Mood Enhancer Prevention) is effective in preventing the onset of major depressive disorder when compared to an online psychoeducation-only control over a 12-months follow-up period. It is expected that depressive symptomatology will be reduced to a greater extend in the intervention group than in the control condition. It is hypothesised that GET.ON Mood Enhancer Prevention is superior in terms of cost-effectiveness, and QALY health gains compared to the psychoeducation-only control.

## Methods/Design

### Design

A two-armed randomised controlled trial (RCT) will be conducted to compare GET.ON Mood Enhancer Prevention with a psychoeducation-only control condition. Measurements will be taken at baseline, post-treatment (6 weeks), 6, and 12 months follow-up (after randomisation). Telephone-administered Semi-Structured Diagnostic Interviews (SCID) will be conducted at baseline, 6- and 12-months follow-up with the SCID/DSM-IV section for mood disorders (see Figure 1 for a detailed overview of the study design). The study is approved by the Medical Ethics Committee of the Philipps University Marburg (No. 2012-35 K).

**Figure 1 F1:**
[figure not shown]
Overview of study procedure.

### Inclusion and exclusion criteria

We will include adults (a) age 18 and above who (b) suffer from subthreshold depression (Centre for Epidemiological Studies Depression Scale (CES-D) ≥ 16) but do not meet DSM-IV criteria for a major depressive episode, (c) have Internet access, and (d) are willing to give informed consent. We will exclude subjects who (a) meet DSM-IV criteria for (a) current major depressive episode, (b) a bipolar disorder, or (c) a psychotic disorder. Additional exclusion criteria are: (d) a history of a major depressive disorder in the past six months (based on Kupfer [35]), (e) currently receiving psychotherapy for any kind of mental health problems, (f) being on a waiting list for psychotherapy, (g) receiving psychotherapy in the past six months, and (h) showing a notable suicidal risk, as indicated through a score greater 1 in the Beck Depression Inventory (BDI) Item 9 (“I feel I would be better off dead”).

### Recruitment

Participants will be recruited from March 2013 to February 2014 via the GET.ON research website [36] that is announced in newspapers, on-air media and related websites. The research website provides information about the GET.ON Mood Enhancer Prevention training and details about the study. Additionally, a major health insurance company will support the recruitment by placing the information leaflet on its website. Individuals interested in participating in the study can apply online on the GET.ON research website by providing the research team with their e-mail address or by sending directly an e-mail to the research team. They do not need to be referred by their GP or other mental health care specialist.

### Assessment of eligibility and randomisation

People who apply online for study participation receive an information letter via e-mail with detailed information about the study procedures. They will be informed that they can withdraw from the intervention and/or study at any time without any negative consequences. Applicants who still want to participate in the study are asked to complete online screening questionnaires including information about the severity of their depressive symptoms (CES-D ≥ 16), whether they are currently receiving any kind of treatment for any mental health disease, whether they are on a waiting list for such a treatment, whether they received such a treatment in the past six months, and whether they have a high suicidal risk (BDI Item 9 > 1). Subjects screened positive and who are willing to give informed consent are scheduled for a semi-structured clinical interview (SCID) conducted by telephone [37,38]. Participants meeting all of the inclusion and none of the exclusion criteria who have completed the baseline assessment and returned the informed consent form via post or e-mail will enter the study and will be randomly allocated to study conditions. Randomisation will take place at an individual level. Block randomisation will be used to ensure equity of ample sizes across study conditions. Random blocks will consist of two allocations each. The allocation will be done by an independent researcher not otherwise involved in the study using an automated computer-generated random numbers table.

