### Blinding

The research staff conducting the semi-structured clinical interviews at 6- and 12-months follow-up will be blinded to the condition the participants are assigned to. These include: (a) an explanation to the participants why it is important not to inform the interviewer about the condition they were assigned to; (b) a written reminder for the interviewer in the interview manual to ask the participant not to inform him/her about the randomisation status; (c) written and verbal reminders to the patient before each interview; and (d) a documentation after each assessment of whether or not the interviewer is still blind to treatment condition. With regard to the latter, the interviewer will be asked to guess each participant’s randomisation status and these guesses will be compared with the actual status. Cohen’s kappa will be computed to clarify whether hit rates differ from what can be expected from chance. In case of evidence for blinding break down, the interviewer will be changed to the second outcome interview.

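### A published, constant block size of two makes half of the 406 allocations certain to anyone who knows the preceding allocation and the entry order

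*Protocol article*

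**What the plan says.** All the randomisation rules stand in the protocol article under Assessment of eligibility and randomisation. The unit is the participant: "Randomisation will take place at an individual level". The reason for blocking is balance: "Block randomisation will be used to ensure equity of ample sizes across study conditions". The block size is then fixed: "Random blocks will consist of two allocations each". No strata are mentioned.

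Two safeguards are given. Allocation comes last, for participants "who have completed the baseline assessment and returned the informed consent form via post or e-mail will enter the study". It is also kept apart from the trial team: "The allocation will be done by an independent researcher not otherwise involved in the study using an automated computer-generated random numbers table".

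The Blinding section covers the outcome assessors: "The research staff conducting the semi-structured clinical interviews at 6- and 12-months follow-up will be blinded to the condition the participants are assigned to". Its measures are instructions and reminders not to disclose the arm, "a documentation after each assessment of whether or not the interviewer is still blind to treatment condition", a test of interviewers' guesses against chance with Cohen's kappa, and a change of interviewer for the second outcome interview if blinding fails.

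The Intervention section shows that the arms look different to those involved. The training arm has an online trainer; the psychoeducation arm has no trainer support.

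**The concern.** Concealment has two parts. The list must be kept from those who enrol, and the next assignment must not be deducible from assignments already known. Independent allocation deals with the first. A constant block of two works against the second: once the first arm of a pair is known, nothing random is left in the second. Publishing the block size tells everyone that this is so.

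This matters more here than in a double-blind trial. The arms are visible to participants, and trainers know whom they support, so individual allocations can become known during recruitment. Eligibility depends partly on a semi-structured SCID that separates subthreshold depression from a major depressive episode, which leaves room for judgement. The primary outcome, time to onset of MDD, is also an interviewer's rating from the SCID and life charts. Foreknowledge at entry could allow selective enrolment, and knowledge of the arm at follow-up could colour the rating. The measures in the Blinding section address disclosure by participants and detection of lost blinding. None addresses inference from the sequence.

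**Working it through.** The document gives no figure for predictability, so there is none to reproduce.

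**Inputs**
- Block size 2, the same throughout (Assessment of eligibility and randomisation).
- Equal arms, so one allocation to each arm per block (same section, from the stated purpose of blocking).
- Total N = 406 (Sample size calculation), so 406 / 2 = 203 blocks.
- Assumption: one unstratified sequence, since no strata are stated.
- Assumption: the observer knows the block size, all earlier allocations and the order of entry. For blocks of two, the preceding allocation and the place in the sequence are enough.

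**Formulas**, for a 1:1 permuted block of size 2m:
- Expected share of allocations that are certain = 1/(m + 1).
- Expected correct guesses per block, always guessing the arm that is behind and tossing a coin at a tie = m + (2^(2m)/C(2m, m) − 1)/2. Dividing by 2m gives the share guessed correctly.

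**Block of two (m = 1)**
- Certain: 1/(1 + 1) = 50%, and 0.50 × 406 = 203 allocations.
- Correct guesses per block: 1 + (4/2 − 1)/2 = 1.5, and 1.5/2 = 75%. Over the trial, 0.75 × 406 = 304.5, against 203 expected by chance.
- A simulation of 406 allocations with 4000 repeats gave 75.0%.

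**Comparison, block size known**

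| Block size | Certain | Guessed correctly |
|---|---|---|
| 2 | 50% (203 of 406) | 75.0% |
| 4 | 33.3% | (2 + (16/6 − 1)/2)/4 = 70.8% |
| 6 | 25.0% | (3 + (64/20 − 1)/2)/6 = 68.3% |
| 8 | 20.0% | (4 + (256/70 − 1)/2)/8 = 66.6% |

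**Varying, undisclosed sizes.** By simulation with the same guessing rule, 69.3% are guessed correctly for sizes 4 and 6 mixed, and 68.1% for 4, 6 and 8 mixed. A guesser who does not know the current block size can rarely be certain of an assignment; this last statement is reasoned, not computed.

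**Cost in balance.** If recruitment stops inside a block of 8, the worst case is four allocations to one arm and none to the other, a difference of 4. With N = 406 that is 205 against 201.

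**The case against.** The best defence is that the figures describe an observer whom the document does not show to exist. Three stronger readings are tempting, and none is supported.

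- *A reader might infer that study staff see each allocation as it is made.* The document does not say so. An independent researcher carries out the allocation itself and does not merely prepare a list. A trainer sees the training-arm participants in their care, not the sequence, and trainers are not said to recruit or to judge eligibility.
- *A reader might infer that staff control when a participant enters.* People apply online, complete online screening and return their own consent form, so the moment of entry depends partly on the participant. Some staff influence, for example through interview scheduling, is possible, but control is not shown.
- *A reader might infer that a participant who discloses the arm at interview also unblinds the interviewer to the paired participant.* That requires the 6- or 12-month interviewer to know who was randomised next to whom, which nothing in the document indicates. The guess test would also tend to show a material loss of blinding from any cause, though only after the event.

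Two further points are fair. A condensed article may leave to the full protocol who can see the sequence or the entry order, so that silence is no fault. On best-guess accuracy, the gain from the undisclosed 4, 6 and 8 mix is modest: 75% falls to about 68%, or 7 percentage points.

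These arguments limit the consequence but leave the design rule as it is. The block size is stated outright, so this is not an omitted detail. Protecting the list does not stop inference from an arm that becomes known, and in an open-arm trial some arms will become known. The larger gain from the change is in certainty, which drops from half of all allocations to very few.

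**Conclusion.** The point holds in conditional form. A constant, published block of two is the most predictable 1:1 permuted block there is: 203 of 406 allocations (50%) are certain, and 75% can be guessed, by someone who knows the preceding allocation and the entry order. Independent allocation after eligibility, baseline assessment and consent lessens the risk to concealment without removing it. The risk to the follow-up interviewers' blinding is indirect and arises only if they know the entry order.

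The document does not show that concealment or blinding has failed, or that selection bias has occurred. This is an avoidable weakness that should be corrected. The figures assume 1:1 allocation in a single unstratified sequence, with the stated size read as two allocations per block.

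**What to change.** For all remaining allocations, replace the blocks of two with permuted blocks of larger, randomly varying size, for example 4, 6 and 8. Withhold the block sizes and the entry order from recruiting, interviewing and coaching staff, and do not publish the sizes while recruitment is open. Keep the independent researcher and the present timing of allocation.

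The cost is a new computer-generated list and a possible final imbalance of up to about 4 participants in 406, which preserves the aim of equal arms for practical purposes.

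The stated recruitment period is March 2013 to February 2014. If recruitment is complete, the list cannot be changed. In that case, report who had access to allocations and to the entry order, and in particular whether anyone conducting baseline or follow-up SCIDs did, and state the predictability of the sequence as a limitation.

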### Blinding

The research staff conducting the semi-structured clinical interviews at 6- and 12-months follow-up will be blinded to the condition the participants are assigned to. These include: (a) an explanation to the participants why it is important not to inform the interviewer about the condition they were assigned to; (b) a written reminder for the interviewer in the interview manual to ask the participant not to inform him/her about the randomisation status; (c) written and verbal reminders to the patient before each interview; and (d) a documentation after each assessment of whether or not the interviewer is still blind to treatment condition. With regard to the latter, the interviewer will be asked to guess each participant’s randomisation status and these guesses will be compared with the actual status. Cohen’s kappa will be computed to clarify whether hit rates differ from what can be expected from chance. In case of evidence for blinding break down, the interviewer will be changed to the second outcome interview.

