### Sample size calculation

We assume an absolute risk reduction of at least 10% for the incidence of major depressive disorder (MDD) between intervention and control group as clinically relevant. Based on previous studies evaluating interventions directed at the prevention of MDD, we expect a mean incidence of MDD in the control group of 25% within the 12-months follow-up period [48-50]. Based on a power of 80%, an alpha of 0.05, a relative risk reduction of 40%, and an attrition rate of 20%, we will need 406 participants to demonstrate an absolute risk reduction of 10% between the groups using log rank survival analyses (calculated using PASS 12).

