#### Primary outcome

The primary outcome is time to onset of MDD within a 12-months follow-up period. Major depressive disorder will be assessed according to DSM-IV criteria as assessed by the telephone-administered Structured Clinical Interview for DSM-IV (SCID) at 6 and 12 months [37,38]. The inter-rater agreement of the Axis I disorders is moderate to excellent [51]. The agreement between face-to-face and telephone SCID interviews as indicated by the kappa coefficient is considered to be excellent [52]. Time to onset of MDD will be assessed using life charts. Life events are recalled by using a calendar method after which the presence of depressive symptoms at each month during the follow-up period is determined. SCIDs will be conducted by trained psychologists who are blind to treatment condition. The interviews will be recorded to examine inter-rater reliability. Disagreement shall be solved by discussion and the agreed rating will be used for analysis. If this is not possible, the assessment will be rated by an experienced psychotherapist (gold standard) and this rating will be used for analysis.

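### The arm guess is recorded after the outcome interview, so an above-chance kappa can reflect efficacy as well as loss of blinding, and the overall kappa cannot tell them apart

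*Protocol article*

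**What the plan says.** The Blinding section of the protocol article lists, among its safeguards, "a documentation after each assessment of whether or not the interviewer is still blind to treatment condition". It then specifies how: "the interviewer will be asked to guess each participant’s randomisation status and these guesses will be compared with the actual status". Agreement between guess and arm is to be summarised by a kappa coefficient, whose purpose is given in these words: it "will be computed to clarify whether hit rates differ from what can be expected from chance". The stated consequence is: "In case of evidence for blinding break down, the interviewer will be changed to the second outcome interview".

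The person guessing is the outcome assessor. Under Primary outcome the article states: "SCIDs will be conducted by trained psychologists who are blind to treatment condition".

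The text does not place the guess before the symptom questions, ask for its reason, condition kappa on MDD status or give a kappa threshold. It does not say whether kappa is computed per interviewer or over all interviews. Nothing under Statistical analyses ties the primary analysis to the result.

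**The concern.** The check is meant to show whether interviewers learned the allocation. At the moment of guessing, however, the interviewer knows whether the participant developed MDD and how the symptoms went. An interviewer who leans towards 'control' for people who became depressed will be right more often than chance whenever the intervention prevents depression, without any leak. Above-chance agreement therefore has two possible explanations, and the planned statistic does not distinguish them.

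The main stake is interpretation. MDD is interviewer-rated, so blinded assessment protects the primary outcome. A trial with a real effect could have to report guesses better than chance and be unable to say whether that reflects assessor bias or efficacy. A lesser stake is a needless change of interviewer for the second outcome interview.

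**Working it through.** **Inputs from the protocol article**
- Control risk (Sample size calculation): "we expect a mean incidence of MDD in the control group of 25% within the 12-months follow-up period".
- Intervention risk: the same section gives a relative reduction of 40% and an absolute reduction of 10%. These agree: 25% × (1 − 0.40) = 15%, and 25% − 15% = 10 points.
- Numbers assessed: 406 with 20% attrition gives 406 × 0.8 = 324.8, taken as 163 per arm.
- Allocation: 1:1, in blocks of two (Assessment of eligibility and randomisation).

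The Blinding section states no figure of its own to reproduce.

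**Assumptions**
- Blinding is intact, so guesses use only what the interview reveals about outcome.
- The hazard is constant, so 6-month risks are 1 − 0.75^0.5 = 13.4% and 1 − 0.85^0.5 = 7.8%.
- The test is two-sided at 0.05. The article does not state sidedness for kappa.
- There are two guessing rules. *Strict*: cases are guessed 'control' and non-cases 'intervention'. *Weak*: cases are guessed 'control' and non-cases by coin toss.

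**Kappa**

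Let qC and qI be the probabilities of guessing 'control' in the control and intervention arms. With 1:1 allocation, chance agreement is 0.5 and observed agreement is ½[qC + (1 − qI)]. Hence kappa = (observed − 0.5)/0.5 = qC − qI.

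**Flag rate**

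The flag rate is approximately Φ[(qC − qI − 1.96·SE0)/SE1], plus the negligible or small opposite tail. SE0 uses the pooled proportion and SE1 the separate proportions, each with 163 per arm.

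| Time, rule | qC | qI | kappa | SE0 | SE1 | flag rate |
|---|---|---|---|---|---|---|
| 6 months, weak | 0.567 | 0.539 | 0.028 | 0.0551 | 0.0551 | 8% |
| 6 months, strict | 0.134 | 0.078 | 0.056 | 0.0341 | 0.0340 | 37–38% |
| 12 months, weak | 0.625 | 0.575 | 0.05 | 0.0543 | 0.0542 | 15% |
| 12 months, strict | 0.25 | 0.15 | 0.10 | 0.0443 | 0.0440 | 62% |

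Example, 12 months strict: (0.10 − 1.96 × 0.0443)/0.0440 = 0.30, and Φ(0.30) = 0.62. The hit rate is (0.25 + 0.85)/2 = 55%. Simulation with the null standard error of kappa gives the same flag rates, and 5% when there is no treatment effect.

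**Sensitivity**
- One-sided testing: about 13% (weak) to 50% (strict) at 6 months, and 23% to 73% at 12 months.
- Kappa per interviewer, strict rule, assuming 40 to 160 interviews each: about 7–20% at 6 months and 12–36% at 12 months.
- Guessing by symptom severity: take a latent symptom score with MDD as its upper tail. A 0.36 SD shift turns 25% into 15%. If guesses are a median split of the score, an overall check is flagged about 73% of the time. A Mantel-Haenszel check stratified by MDD is still flagged about 40% of the time.

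**The case against.** The strongest reply is that nothing shows interviewers guess in the way the high figures need. The strict rule means about 80% 'intervention' guesses at 12 months (1 − (0.25 + 0.15)/2) and about 89% at 6 months, in a 1:1 trial. A reader might infer that an effective intervention would usually be reported as a blinding failure. The article does not support that: under the weak rule the false-flag rate is 8% or 15%. This part of the reply stands.

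The timing point also stands. The interviewer change concerns the second outcome interview, so only the 6-month check can trigger it and the 12-month figures bear on reporting only. The 12-month strict figure further assumes that the interviewer sees the whole year's outcome. Statistical analyses has participants who missed the 6-month assessment asked back to baseline. That may imply that others are asked only about the interval since 6 months, although Primary outcome is not explicit. Interval risks would then be 25% − 13.4% = 11.6% and 15% − 7.8% = 7.2%. Strict kappa would be about 0.04, with a flag rate of about 27–28%.

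The harm is limited. A false alarm leads to a swap of interviewer. The article does not say that kappa alone counts as breakdown, and blinding status is also to be documented. That documentation, however, is put into operation through the guess.

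It could be said that such detail belongs in the full protocol or the interview manual. That does not answer the point: the article itself fixes a guess after the assessment and a comparison with chance, and that rule is what confounds the two explanations.

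**Conclusion.** The point holds as a flaw in how the blinding check is read. Under a real treatment effect, a guess informed by the outcome exceeds chance without unblinding, and the overall kappa cannot separate this from a leak. At the trial's own design effect the false-flag rate is about 8% to 38% at 6 months and about 15% to 62% at 12 months, against 5% with no effect. These ranges rest on assumed MDD-based guessing rules, a constant hazard for the 6-month risks, pooled interviews and a two-sided test. Expected kappa is only 0.03 to 0.10, so the difficulty lies in testing against chance rather than in a large apparent agreement.

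Two stronger readings should be avoided. The documents do not show that a false flag is the likely result, and they give no ground for saying that the primary analysis would change or be biased by one. This is a low-cost improvement to a secondary check.

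**What to change.** - Have the interviewer record, with each guess, its reason: participant disclosure; another cue to the arm, such as mention of a trainer or homework; symptom course; or pure guess.
- Report kappa within the MDD-yes and MDD-no strata beside the overall kappa.
- State that an above-chance overall kappa alone is not evidence of blinding breakdown. Rely on guesses attributed to disclosure or other arm-specific cues. Counting disclosure only would miss indirect leaks.
- Where feasible, also record a guess before the symptom questions.

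The cost is one extra form item (and a second guess where an early one is taken) and a stratified version of a planned statistic. Kappa in the small MDD-yes stratum will be imprecise. Stratifying by MDD brings the false-flag rate back to about 5% only if guesses depend on MDD status alone. Where severity also informs them, part of the confounding remains, which is why the recorded reason matters.
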